### Interventions

When randomized to the preventive nebulization arm, the patient will receive nebulization every 6 hours with solutions containing 300 mg acetylcysteine *plus* 2.5 mg salbutamol. Flasks of acetylcysteine and salbutamol are provided by the pharmacy of the participating center. Since no placebo will be used, labeling of the drugs is not necessary. Solutions are nebulized using jet nebulizers or vibrating mesh nebulizers, depending on local availability in the participating centers. Nebulizers are set according to manufacturer’s recommendations. External nebulizers are powered by pressured air or oxygen at a continuous flow of 3 to 5 L/min. The nebulizer will be attached to the tubing system, always after the heated humidifier or the heat and moisture exchange (HME) filter (that is, at the side of the patient). A nebulization session typically lasts 20 to 30 minutes. The type of nebulizer used will be recorded in the case record form (CRF).

When randomized to the nebulization on indication arm, nebulization of acetylcysteine *or* salbutamol is restricted. The doctor staff can decide to order nebulization of solutions containing 300 mg acetylcysteine *or* 2.5 mg salbutamol in case a patient has persistent thick and tenacious secretions [26] or in cases of bronchospasm (suspected when there is a clinical wheezing, and signs of obstruction of the lower airways on ventilator waves or the end-tidal CO_2_ curve), respectively. Daily reassessment of the indications mentioned above will reassure that nebulization is stopped when no longer needed. The decision to start and stop nebulization is recorded in the CRF.

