### Standard airway care

Independent ICU physicians and nurses not involved in the trial perform standard airway care, including endotracheal suctioning, humidification of inhaled air and tracheostomy placement.

Endotracheal suction is performed when clinically indicated and according to the local guidelines [46]. Normal saline instillation prior to endotracheal suction will not be used [46]. The use of an open or closed endotracheal suction system is left to the discretion of the participating center and will be recorded in the CRF.

Humidification and heating method of the inhaled air is left to the discretion of the participating center and will be recorded in the CRF. Active humidification of the air inhaled will be supplied by the use of an electrically powered humidifier. Passive humidification of the air inhaled will be supplied by the use of a heat and moisture exchange filter.

Tracheostomy is considered on indications only and preferably not in the first ten days after intubation [47]. Indications for tracheostomy are failure to intubate, expected duration of ventilation >14 days, Glasgow Coma Score <7 and/or inadequate swallow or cough reflex with retention of sputum, severe ICU acquired weakness, prolonged or unsuccessful weaning and repeated respiratory failure after tracheal extubation.

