### Data analysis

The main analysis will compare the number of ventilator-free days and survival to day 28 between the two randomized groups. If the non inferiority of nebulization on indication compared to preventive nebulization can be confirmed, the superiority of nebulization on indication compared to preventive nebulization for the primary endpoint will be tested.

In addition, we will analyze the non inferiority between the two treatment groups regarding their survival distributions. Considering that survival times are not normally distributed and because some survival times will be censored by mortality, the Cox proportional-hazards model will be used to analyze the data. Significance will be expressed by the standard log rank test.

The effect of preventive nebulization on the primary outcome will also be investigated in prespecified subgroups based on patient categories (namely, patients with pneumonia versus patients without pneumonia and surgical versus medical admissions), and will be adjusted for the type of nebulizer (jet nebulizer or vibrating mesh), humidification method (active or passive), and type of flow used for nebulization (continues with external source or breath synchronized with an inline flow from the ventilator).

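### The additional adjusted analysis of the primary outcome uses nebulizer type and nebulization flow as covariates; if taken as used, they are undefined for on-indication patients never nebulized and can bias that estimate

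*Protocol article*

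**What the plan says.** The Data analysis section states the main analysis first and without covariates: "The main analysis will compare the number of ventilator-free days and survival to day 28 between the two randomized groups". A later paragraph turns to additional work. The effect on the primary outcome will also be examined in subgroups (pneumonia or not, surgical or medical) and "will be adjusted for the type of nebulizer (jet nebulizer or vibrating mesh), humidification method (active or passive"), and for "type of flow used for nebulization (continues with external source or breath synchronized with an inline flow from the ventilator").

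Three other places bear on what these covariates mean:

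- Interventions, on the device: "Solutions are nebulized using jet nebulizers or vibrating mesh nebulizers, depending on local availability in the participating centers". On its recording: "The type of nebulizer used will be recorded in the case record form (CRF").
- Interventions, on the on-indication arm: acetylcysteine or salbutamol may be ordered only for persistent thick secretions or for bronchospasm, and "Daily reassessment of the indications mentioned above will reassure that nebulization is stopped when no longer needed".
- Standard airway care, on humidification: "Humidification and heating method of the inhaled air is left to the discretion of the participating center and will be recorded in the CRF".

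The Discussion adds that nebulizer and humidifier type may influence how much drug reaches the lung. It names stratification of randomization by center as the control, and refers to data collection and subgroup analyses as well. No section says whether nebulizer type and flow enter the model by patient or by center, or what value a patient who is never nebulized receives.

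**The concern.** Nebulizer type and flow are properties of a delivered nebulization. In the preventive arm, with nebulization every 6 hours, essentially every patient has both. In the on-indication arm a patient has them only after an indication has arisen. The listed levels (jet or mesh; continuous or breath-synchronized) have no place for the others.

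An analyst who follows the sentence with the recorded data has two routes. One is a complete-case model, which drops the never-nebulized on-indication patients. The other is an added level for no nebulizer, which occurs essentially in one arm and takes up part of the treatment contrast. In both, the adjusted coefficient compares all preventive patients with the on-indication patients who developed thick secretions or bronchospasm.

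At stake is the credibility of one supplementary estimate of the primary outcome. It could appear to contradict a valid non-inferiority result, and a reader could take the adjusted figure as the better one because it seems to account for device differences.

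**Working it through.** The plan gives no figure for this point, so there is none to reproduce. The check asks when bias arises and how large it could be.

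**1. Both codings, no true treatment effect.** Taken from the document: 950 patients, 1:1 allocation, seven centers, nebulizer type set by the center. Assumed: SD of ventilator-free days (VFD) about 9; a share p = 20%, 40% or 60% of on-indication patients ever nebulized; VFD falling by b = 0, 2 or 4 days per SD of a severity factor; that factor correlated 0.7 with the tendency to be nebulized. Mean bias in favor of preventive nebulization over 400 simulated trials per setting:

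| p | b | Unadjusted, or device coded by center | Device as used (patients dropped, or a 'none' level) |
|---|---|---|---|
| 20% | 0 | 0.00 | 0.00 |
| 20% | 2 | 0.00 | 2.04 |
| 20% | 4 | 0.02 | 3.95 |
| 40% | 0 | -0.01 | -0.01 |
| 40% | 2 | 0.01 | 1.35 |
| 40% | 4 | 0.01 | 2.77 |
| 60% | 0 | -0.03 | -0.03 |
| 60% | 2 | -0.04 | 0.84 |
| 60% | 4 | -0.04 | 1.78 |

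**2. Check by formula.** The mean severity of nebulized on-indication patients is 0.7 × φ(z)/p, with z the upper p point and φ the density of the standard normal distribution. The bias is b times that.

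- p = 20%: 0.7 × 0.280/0.2 = 0.98, giving 1.96 days (b = 2) and 3.92 days (b = 4).
- p = 40%: 0.7 × 0.386/0.4 = 0.676, giving 1.35 and 2.70.
- p = 60%: 0.7 × 0.386/0.6 = 0.451, giving 0.90 and 1.80.

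These agree with the simulation.

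**3. Precision.** With a 'none' level, only the nebulized share p of the on-indication arm informs the treatment effect. Its variance rises by about (1 + 1/p)/2: 3.0 at 20%, 1.75 at 40%, 1.33 at 60%. The simulation gave 3.0, 1.8 and 1.3.

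**4. Is a link between nebulization and outcome plausible?** Bias under as-used coding needs one. The design supplies one without any severity effect: an on-indication patient stays at risk of an indication until extubation, and longer ventilation means fewer VFD. To illustrate, take ventilation duration as lognormal with mean 5 days and coefficient of variation 0.7 (Sample size calculation). Assume a constant hazard of a first indication of 0.08 to 0.25 per day, unrelated to severity.

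- Never nebulized: 69% (hazard 0.08) to 36% (hazard 0.25) of the arm.
- VFD gap, never minus ever nebulized: 2.4 to 2.5 days with no deaths, 1.8 to 1.9 days with an assumed 25% mortality.
- Shift of the on-indication mean when the never-nebulized are dropped = -(share never nebulized) × gap. The extremes are -0.69 × 2.42 = -1.7 (hazard 0.08, no deaths) and -0.36 × 1.90 = -0.7 (hazard 0.25, 25% mortality).

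**The case against.** The strongest reply is that the article does not commit to as-used coding. It says the device depends on local availability and humidification on the center, and the Discussion treats both as differences between centers, handled by stratification. A center-level value exists for every patient and gives no bias, as the table shows. Coding detail is also commonly left to an analysis plan, which is not shown here.

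Much of this stands. A reader might infer that the adjusted effect is bound to be biased; the text does not support that, because bias needs both as-used coding and a link between being nebulized and outcome. A reader might also infer that the randomized comparison itself is lost. It is not: the main comparison carries no covariates and General statistical considerations makes intention-to-treat the initial analysis. Nor does the concern extend to humidification as an undefined value, since it applies to ventilated patients in both arms; no section says that it changes in response to secretions.

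A comparison with the 10% margin is tempting too, but the documents give no mean number of VFD from which to turn 10% into days. Finally, the likely direction works against the trial's own claim, so this adjustment would not be expected to produce a false finding of non-inferiority.

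What the reply does not remove is that the article itself names these treatment-delivery variables as covariates, speaks of the flow and device used, and nowhere codes either by center. No section says that the center determines the flow mode; the remark that external nebulizers run on continuous flow links it at most to the device.

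**Conclusion.** The point holds for the additional adjusted analysis only. If nebulizer type and flow are entered as used, they condition on treatment delivered after randomization. They then either exclude never-nebulized on-indication patients or isolate them in a level found essentially in one arm. The estimate is then biased, probably against nebulization on indication. The illustrations give roughly 0.8 to 4.0 VFD when severity drives nebulization, and 0.7 to 1.7 VFD from time at risk alone. The share nebulized, the VFD spread, the strength of the severity link, the hazard of an indication and the mortality are all assumptions, so these figures show the order of size and are not predictions. With center-level coding the bias is about zero. The primary non-inferiority conclusion does not depend on this. The sentence should be corrected before analysis, but it is not a threat to the main result.

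**What to change.** Do not use as-used nebulizer type or flow as covariates. Adjust for center, which is already the stratification factor. Alternatively, record each center's standard nebulizer and flow mode as center-level attributes that every patient carries from before randomization, and use them, for example, to examine treatment-by-attribute interaction. Humidification may stay if it is defined as the center's practice or the value at randomization. The device and flow actually used can still be reported descriptively among nebulized patients. If center-level coding was intended all along, one sentence saying so is enough.

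The cost is a change of wording in the analysis plan and one short entry per center for the standard device and flow mode. No new patient data, no change of sample size and no change to the main analysis are needed.

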### General statistical considerations

Initial analyses will be performed according to the intention-to-treat (ITT) method. In addition, per-protocol (PP) analysis, including only those patients who complete the treatment according to the originally allocated protocol, will be done to check for the robustness of the results.

Continuous normally distributed variables will be expressed by their mean and standard deviation, or when not normally distributed as medians and their interquartile ranges. Categorical variables will be expressed as counts (n) and percentages (%). To analyze differences in continuous variables between the two groups, Student’s t-test will be used, or in case continuous data is not normally distributed, the Mann–Whitney U test will be used. Categorical variables will be compared with the Chi-square test or Fisher's exact tests. Statistical significance is considered to be at a *P* value <0.05 with one or two side test, depending on assessment of either non inferiority or superiority. The ICU mortality, hospital mortality, the length of ICU stay, and the length of hospital stay will be expressed with Kaplan-Meier curves.

When appropriate, statistical uncertainty will be expressed by 95 % confidence levels. All statistical analyses will be performed with the R language and environment for statistical computing [53].

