### Primary outcome and secondary outcomes of the trial

The primary outcome of this study is the number of ventilator-free days (VFD) and survival to day 28, defined as the number of calendar days of unassisted breathing, after both ICU admission and start of mechanical ventilation to day 28, if the period of unassisted breathing lasted at least 24 consecutive hours. Unassisted breathing is defined as being extubated, ventilating with or without facemask, nasal prong oxygen, room air or tracheostomy breathing, but always without continuous positive airway pressure or pressure support of intermittent mandatory ventilation assistance. Patients who die before 28 days or are mechanically ventilated longer than 28 days are assigned zero ventilator-free days.

Secondary outcomes include clinical endpoints and cost-effectiveness outcomes. Clinical endpoints include the following: ICU and hospital length of stay (LOS); ICU, hospital, and 90-day mortality; development of moderate or severe ARDS; ventilator-associated pneumonia (VAP); development of atelectasis and pneumothorax; incidence of obstruction of the endotracheal tube (wherefore endotracheal tube exchange is indispensable); cumulative dose and duration of sedatives, cumulative dose and duration of neuromuscular blocking agents, development of delirium and incidence of side effects of nebulization of acetylcysteine and/or salbutamol. In addition, related healthcare costs will be compared from a health systems perspective over the time horizon of the trial and include direct medical and indirect costs of days of mechanical ventilation, stay in the ICU and hospital, cumulative use of sedatives and neuromuscular blocking agents, tracheostomies and ventilator-associated pneumonia.

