### Sample size calculation

Randomized trials assessing the efficacy of preventive nebulization are absent, which hampered power calculations. Therefore, the sample size calculation, based on a non-inferiority design, is calculated using the mean duration of invasive ventilation and the associated coefficient of variation, respectively 5 and 0.7 (log-transformed data) days [52], with a noninferiority margin of 10 %. A maximum difference in clinical effectiveness of 10 % between the ‘nebulization on indication’ arm as compared to the ‘preventive nebulization’ arm will be tolerated to consider a strategy of ‘nebulization on indication’ not to be inferior, with regard to the primary endpoint ventilator free days. Using these assumptions associated with the study design, a one-sided type I error of 0.05 and 80 % power (type II error), yields a sample size of 950 patients, which includes a 5 % anticipated drop out.

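### The general test rule sends ventilator-free days to a Mann–Whitney test that contains no 10% margin, so it cannot decide non-inferiority

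*Protocol article*

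**What the plan says.** All references are to the protocol article.

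- **Endpoint** (Primary outcome and secondary outcomes of the trial), where the definition opens with: "The primary outcome of this study is the number of ventilator-free days (VFD) and survival to day 28". On scoring: "Patients who die before 28 days or are mechanically ventilated longer than 28 days are assigned zero ventilator-free days". Days are calendar days.
- **Margin** (Sample size calculation): "A maximum difference in clinical effectiveness of 10 % between the ‘nebulization on indication’ arm as compared to the ‘preventive nebulization’ arm will be tolerated". The section applies this to ventilator-free days. The calculation uses "a one-sided type I error of 0.05" and 80% power, and gives 950 patients including 5% dropout.
- **Main analysis** (Data analysis): "The main analysis will compare the number of ventilator-free days and survival to day 28 between the two randomized groups". If non-inferiority is confirmed, superiority follows. No test is named here for VFD. The Cox model and log-rank test belong to an additional analysis of survival distributions.
- **Test rule** (General statistical considerations): continuous variables are compared by Student's t-test, "or in case continuous data is not normally distributed, the Mann–Whitney U test will be used". The P threshold of 0.05 applies "with one or two side test, depending on assessment of either non inferiority or superiority".

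**The concern.** VFD as defined has a block of zeros (deaths and ventilation beyond 28 days). Given the planning mean of 5 days on the ventilator, it also has a cluster of survivors near 23 days. Even among survivors, 28 minus a log-normal duration is skewed. The normality condition therefore fails and the rule selects Mann–Whitney. Because the same paragraph links its one-sided P value to non-inferiority, the article does more than stay silent: it names a test that does not address the stated hypothesis. The hypothesis is that no more than 10% of VFD is lost, whereas Mann–Whitney tests whether the two distributions are equal.

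The trial's one confirmatory decision is at stake. Taken literally, the rule has almost no chance of confirming non-inferiority when the arms are equal. An analyst who notices this will probably add the margin to the rank test, and the obvious ways of doing so are insensitive to extra deaths, which is one of the ways the on-indication arm could be worse.

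**Working it through.** **1. The plan's own figure.** On the log scale, SD = √ln(1 + 0.7²) = 0.6315 and margin = −ln(0.9) = 0.1054. Then n per arm = 2 × 0.6315² × (1.645 + 0.842)² / 0.1054² ≈ 445, or 890 in total, and 890/0.95 = 937. That is close to the stated 950, so the sample size reproduces and is not in dispute. Evaluable patients: 950 × 0.95 / 2 ≈ 451 per arm.

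**2. Simulation set-up.** Ventilation time is log-normal with mean 5 days and CV 0.7 (from the article), rounded up to calendar days. VFD = 28 − duration, not below 0, and VFD = 0 for deaths. There are 451 per arm and the test level is one-sided 0.05. The article gives no mortality, so control mortality is an assumption, varied from 10% to 40%. The margin is 10% of the control mean VFD.

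Procedures compared:
- difference in means: (ȳ − x̄ + margin)/SE > 1.645;
- shifted Mann–Whitney: on-indication values plus the margin, against control. Where the Hodges–Lehmann lower limit was also compared with the margin, it gave the same rates;
- scaled Mann–Whitney: on-indication values against 0.9 × control values;
- plain one-sided Mann–Whitney, with no margin.

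**3. True 10% loss of mean VFD through deaths only** (non-inferiority should be declared in 5%; 2,000 trials per row):

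| Control vs on-indication mortality | Control mean VFD | Margin (days) | Mean difference | Shifted | Scaled | Plain |
|---|---|---|---|---|---|---|
| 10% vs 19% | 20.3 | 2.03 | 5.4% | 100% | 100% | 0% |
| 25% vs 32.5% | 16.9 | 1.69 | 4.5% | 99.8% | 99.9% | 0% |
| 40% vs 46% | 13.5 | 1.35 | 4.4% | 100% | 87% | 0% |

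The reason is that a shift breaks every zero–zero tie in favour of the on-indication arm, while the closely spaced survivors dominate the remaining pairs. At 30% mortality the median Hodges–Lehmann shift is 0 days although the mean has fallen by 1.6.

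**4. The same loss through longer ventilation** (25% mortality in both arms, duration × 1.46, loss 10.0%; 1,000 trials): mean difference 5.5%, shifted 28%, scaled 59%.

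**5. Equal arms** (2,000 trials per mortality level): the plain one-sided Mann–Whitney succeeds in 4.9%, 5.4% and 4.7% of trials at 10%, 25% and 40% mortality.

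**6. Power of the mean difference with equal arms.** Power = Φ(margin / (SD × √(2/451)) − 1.645), with √(2/451) = 0.0666:
- 10% mortality: SD 7.5, Φ(2.03/0.499 − 1.645) = 99%;
- 25%: SD 10.2, Φ(1.69/0.679 − 1.645) = 80%;
- 40%: SD 11.3, Φ(1.35/0.755 − 1.645) = 56%.

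**7. Sensitivity.** With ventilation twice as long and more variable, and the loss through deaths at 20–40% mortality, the shifted test declares non-inferiority in 78–100% and the scaled test in 10–32%. The excess depends on the variant and the inputs, but no setting tried brought a rank version with a 10% margin down to 5%.

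**The case against.** The strongest reply is that the rule sits among general considerations for all continuous variables, and that an article may leave the effect measure and the handling of the margin to an analysis plan. That would dispose of a complaint about missing detail. It does not dispose of this one: the article states a rule, ties it to the non-inferiority test, and names no other method for VFD. An analysis plan that is not shown may already override it.

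Three stronger readings are tempting, and the article does not support them.

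- **That the protocol's own rule has a type I error near 100%.** Those rates belong to shifted, scaled or Hodges–Lehmann versions, none of which the article mentions, and they rest on an assumed mortality. The literal plain test errs the other way and almost never confirms non-inferiority.
- **That a non-significant Mann–Whitney result would be read as non-inferiority.** Under a 10% loss through deaths the plain two-sided test is non-significant in roughly 31–62% of trials, but no section equates non-significance with non-inferiority.
- **That 95% intervals contradict the one-sided 0.05 level.** The sentence begins "When appropriate, statistical uncertainty will be expressed by", does not say two-sided, and does not make the interval the decision rule. A one-sided 95% limit agrees with one-sided 0.05.

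It is also fair that loss purely through deaths is the most adverse case, and that excess mortality would be seen in the mortality endpoints, the additional survival analysis and the safety board's reviews. None of these replaces the primary test. Finally, the mean is one defensible estimand among several, but it is one to which a 10% loss of VFD applies directly.

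**Conclusion.** The point holds as a mismatch between the stated test and the stated hypothesis. The zero rule makes VFD non-normal, the general rule then selects Mann–Whitney, and that test has no margin in it. Taken literally, it confirms non-inferiority in about 5% of trials with equal arms, against the planned 80%. Repaired by shifting or scaling, it declares non-inferiority in about 85–100% of trials when 10% of mean VFD is lost through deaths, and in about 30–60% when the loss comes through longer ventilation at 25% mortality. The mean comparison does so in about 4–6%.

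These figures assume 451 per arm, the article's duration inputs and a control mortality of 10–40%, which the article does not give. That Mann–Whitney contains no margin needs none of these assumptions. Because the primary decision depends on it, the wording should be settled before the data are analysed.

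**What to change.** - Exempt the primary endpoint from the normality switch.
- State the estimand: the difference (or ratio) in mean VFD to day 28, on indication versus preventive, with a robust or bootstrap standard error.
- Declare non-inferiority if the one-sided 95% limit, that is the lower limit of the two-sided 90% interval, excludes a 10% loss of mean VFD. Add a note that non-inferiority is read at one-sided 0.05.
- Only then test superiority, at two-sided 0.05.
- Keep Mann–Whitney as a supportive analysis.

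The cost is wording: no new data and no new patients. One downside should be stated openly. The power of the mean comparison depends on mortality: about 99% at 10%, about 80% at 25% and about 56% at 40%. The planned 950 was derived from log duration of ventilation and does not guarantee 80% on this scale.
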